# Clinical effects of atorvastatin combined with conbercept in the treatment of patients with macular edema secondary to retinal vein occlusion and carotid plaque: study protocol for a prospective randomized controlled trial

**DOI:** 10.1186/s13063-024-08082-0

**Published:** 2024-04-08

**Keywords:** Atorvastatin, Anti-vascular endothelial growth factor, Best-corrected visual acuity, Carotid plaques, Central subfield thickness, Intravitreal conbercept, Macular edema, Retinal vein occlusion

## Abstract

**Introduction:**

Intravitreal injections of anti-vascular endothelial growth factor (anti-VEGF) drugs have been widely used in patients with macular edema (ME) secondary to retinal vein occlusion (RVO); however, recurrence is a major concern. This study aims to observe the clinical effects of atorvastatin and intravitreal therapy in the treatment of patients with branch or central RVO-ME and coexistent carotid plaques (CP).

**Methods and analysis:**

A prospective randomized controlled clinical trial will be conducted. Sixty-four patients diagnosed with branch or central RVO-ME and coexistent CP will be enrolled and randomly allocated in a 1:1 ratio to the control and experimental groups. The control group will be treated with intravitreal conbercept monthly for 3 months, followed by monthly evaluation and injection of pro re nata (PRN) for 12 months, while the experimental group will be treated with oral atorvastatin 20 mg daily combined with the control group treatment. If a drop of best-corrected visual acuity (BCVA) is more than five Early Treatment Diabetic Retinopathy Study (ETDRS) letters (one line) or an increment in central subfield thickness (CSFT) of 100 μm (or a 10% increment from the previous visit), intravitreal re-treatment will be performed. Outcome measurements include CSFT, BCVA, number of injections, and incidence of adverse events during the 12-month follow-up period. Differences between groups will be evaluated using Student’s *t*-test, and comparisons between groups will be evaluated using repeated-measures analysis of variance.

**Ethics and dissemination:**

The study has been approved by the Institutional Review Board of Nanjing Lishui People’s Hospital, Nanjing, China (approval number 2023KY0418-12, dated 18 April 2023), and has been registered on chictr.org.cn. Written informed consent will be collected from each patient and the results of this trial will be submitted to a peer-reviewed journal.

**Trial registration:**

Chinese Clinical Trial Registry ChiCTR2300071359. Registered on 12 May 2023.

**Supplementary Information:**

The online version contains supplementary material available at 10.1186/s13063-024-08082-0.

## Introduction

Retinal vein occlusion (RVO) is the second most common retinal vascular disease and is characterized by a sudden painless visual reduction [1, 2]. However, the exact mechanisms underlying RVO remain unclear. Recent evidence has demonstrated that RVO is closely associated with carotid plaques (CP), an important risk factor for stroke [3]. Evidence has confirmed that CP is observed in 54.3% and 76.7% of patients with RVO and branch RVO, respectively [3, 4]. Retinal arteriosclerosis and thrombosis caused by CP can result in retinal venous reflux disorders and secondary RVO [3–5]. RVO can be a predictor of CP and should be evaluated using carotid Doppler ultrasound [1]. Carotid Doppler ultrasound is non-invasive, useful for screening and diagnosing CP, and can accurately evaluate carotid intima-media thickness [3]. However, it is not commonly used for the clinical treatment of RVO.

Macular edema (ME) is the most severe and frequent complication of RVO [2]. Intravitreal injections of anti-vascular endothelial growth factor (anti-VEGF) drugs (e.g., ranibizumab, aflibercept, and conbercept) have been widely used as first-line treatment for patients with RVO-ME [2, 6–8]. However, they have several limitations. First, the clinical effect of anti-VEGF drugs is not long-lasting, and the recurrence of ME indicates repeated injections. Hunt et al. reported that the median number of injections of ranibizumab and aflibercept for branch RVO-ME was seven over 12 months [2]. Sun et al. used conbercept to treat RVO-ME and the mean number of injections was 7.14 ± 1.90 in branch RVO and 7.59 ± 1.39 in central RVO, over 9 months [8]. Second, frequent injections increase surgical risks, including endophthalmitis and secondary glaucoma [6]. Third, anti-VEGF drugs are expensive, and reinjections lead to an economic burden for patients. Therefore, recurrence during follow-up is a major concern for ophthalmologists [7]. Risk factors such as retinal structures (e.g., elevated central retinal thickness and disorganization of retinal inner layers) have been described; however, to the best of our knowledge, investigations of systemic factors such as CP in RVO-ME have not been discussed in the “EURETINA Guidelines for the Diagnosis and Treatment of Retinal Vein Occlusion” [9].

Clinical trials have shown that regular statin use plays a significant role in preventing cerebrovascular atherosclerosis and reducing the risk of cerebrovascular accidents [10]. Atorvastatin, a statin (lipid-lowering drug), has proven to be effective in stabilizing and reversing plaques in patients with carotid atherosclerosis in combination with antiplatelet agents [11–13]. Furthermore, a multicentre study showed that atorvastatin significantly reduced the risk of cardiovascular and cerebrovascular accidents in patients with CP, and the risks of stroke and coronary artery accidents decreased by 33% and 43%, respectively [14].

Recently, atorvastatin has been proven useful in reducing retinal VEGF expression and inhibiting inflammation [15, 16]. Oral atorvastatin was effective in patients with diabetic ME and age-related macular degeneration [17, 18]. Similarly, intravitreal statins can help reduce the development of proliferative vitreoretinopathy [19]. However, clinical investigations of atorvastatin in the treatment of RVO-ME and CP in the current studies are lacking.

## Methods and analysis

### Study objectives

This study aims to observe the clinical effects of atorvastatin and intravitreal therapy in the treatment of patients with branch or central RVO-ME and coexistent CP.

### Trial design

In this trial, 64 patients diagnosed with branch or central RVO-ME and coexistent CP will be enrolled and randomly allocated in a 1:1 ratio to the control and experimental groups. The control group will be treated with intravitreal conbercept (Chengdu Kanghong Pharmaceutical; National Drug Approval No. S20130012), using the 3+ pro re nata (PRN) scheme (monthly for 3 months, followed by monthly evaluation and injection PRN for 12 months) and the experimental group will be treated with oral atorvastatin (Beijing Jialin Pharmaceutical Co., Ltd., GYZZH20093819) 20 mg daily combined with the control group treatment.

### Eligibility criteria

Patients diagnosed with RVO-ME and CP are based on indirect ophthalmoscopy, fundus fluorescein angiography (FFA), spectral-domain optical coherence tomography (SD-OCT), and carotid Doppler ultrasound.

### Inclusion criteria

The inclusion criteria are as follows: (1) patients with a branch or central RVO, aged between 45 and 75 years old; (2) central sub-field thickness (CSFT) > 250 μm, best corrected visual acuity (BCVA) < 0.5; and (3) body mass index < 28 kg/m^2^, carotid stenosis without recanalization surgery.

### Exclusion criteria

The exclusion criteria are as follows: (1) patients with severe cataract, macular membrane, optic neuropathy, glaucoma, and uveitis; (2) patients with a branch or central RVO-ME in both eyes; (3) patients with macular edema secondary to age-related macular degeneration, diabetic retinopathy, Coats disease, Eales disease, or high myopia; (4) history of intravitreal injection, retinal surgery, laser photocoagulation, or ocular trauma; (5) history of taking lipid-lowering drugs in the past month; (6) patients with severe cardiovascular, cerebrovascular, liver, and kidney dysfunction; and (7) patients who cannot tolerate surgery or have poor compliance.

### Withdrawal criteria

The withdrawal criteria are as follows: (1) the follow-up was lost; (2) informed consent was withdrawn; and (3) decision to withdraw for severe adverse events.

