### Masking

Patients and clinicians will be blinded after assignment. The implementation and maintenance of the randomization and masking methods will be completely validated. To avoid evaluation bias, the treatment groups will be hidden from the ophthalmologist who collects the clinical data during each follow-up period. Analysts dealing with the data will also be masked.

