### Primary outcomes

The primary outcome is the average change in CSFT from baseline to 12 months.

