### Safety and combined operation-related adverse events

Possible operation-related complications include elevated intraocular pressure, endophthalmitis, traumatic cataract, vitreous hemorrhage, retinal hemorrhage, retinal detachment, and drug-related adverse events (e.g., liver function damage and gastrointestinal discomfort). In this trial, all the above adverse events and possible causes will be recorded and managed accordingly.

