### Statistical analysis

Data from the patients’ clinical records will be processed using SPSS. For normally distributed data, continuous variables will be expressed as mean ± standard deviation, difference between groups will be evaluated by the Student’s *t*-test, and comparisons inter-group at each endpoint will be evaluated by repeated measures analysis of variance. The Bonferroni method will be used to adjust the overall significance level for multiplicity. For abnormally distributed data, continuous variables will be expressed as M (Q1, Q3), differences between groups will be evaluated using the Mann–Whitney *U* test, and comparisons between groups at each endpoint will be evaluated using a generalized linear mixed model. Categorical variables will be expressed as counts (%), and the chi-square test will be performed. The effect of missing data on the trial results will be assessed using sensitivity analyses of the augmented datasets. Dropouts will be included in the analysis by using modern imputation methods for missing data. The BCVA will be converted to the minimum resolution angle in logarithmic form before data analysis. The clinical data of the branch and central RVO will be sub-analyzed. Two-tailed tests of significance will be performed, and *P*-values < 0.05 will be considered statistically significant.

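### Withdrawal for severe adverse events is not separated from stopping data collection, so obtainable CSFT and safety data may be lost unequally between arms and replaced by imputation

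*Protocol article*

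**What the plan says.** The Withdrawal criteria section of the protocol article has three items: loss to follow-up, withdrawal of consent, and, as item (3), "decision to withdraw for severe adverse events". It has no separate category for a patient who stops a study drug but remains under observation.

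The Statistical analysis section says: "Dropouts will be included in the analysis by using modern imputation methods for missing data". The sentence before it says: "The effect of missing data on the trial results will be assessed using sensitivity analyses of the augmented datasets".

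Under Trial design, the experimental arm receives oral atorvastatin "20 mg daily combined with the control group treatment". The control arm receives conbercept alone, and no placebo tablet is described. Under Masking, the article says: "Patients and clinicians will be blinded after assignment".

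The safety section lists injection complications together with "drug-related adverse events (e.g., liver function damage and gastrointestinal discomfort" and states that "all the above adverse events and possible causes will be recorded and managed accordingly".

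On outcomes: "The primary outcome is the average change in CSFT from baseline to 12 months". Adverse-event incidence over the 12 months is a secondary outcome. Table 1 schedules BCVA, SD-OCT and adverse-event recording every month to month 12, and the Follow-up plan has injections counted at each follow-up.

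**The concern.** Loss to follow-up ends data collection by definition, and withdrawal of consent normally does too. A severe adverse event need not: the patient can usually still attend, have an OCT scan and report further events. Listing it as a third item of the same kind, with nothing to keep the patient in assessment, turns obtainable data into missing data by rule. This is a design matter as well as one for the analysis plan, because a later SAP can choose an imputation model but cannot recover visits that were never made.

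The loss is plausibly related to arm. Both arms carry the risks of injection, and the experimental arm also carries those of a daily oral drug. It is plausibly related to outcome too. A patient who stops atorvastatin may lose whatever benefit it gave, and some listed injection complications, such as endophthalmitis and retinal detachment, affect the eye itself. If the imputation model treats these patients like those who continued, the month-12 contrast can be wrong. On safety, the later course of patients who have already had a severe event is not observed.

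**Working it through.** **Inputs from the documents (Sample size calculation).** Planned difference δ = 263.72 − 241.17 = 22.55 μm; SD used = 30.63 μm; two-sided 5% level; 80% power; 1:1 allocation; 10% loss; 32 per arm.

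**The plan's own figure.** n = 2 × (1.96 + 0.84)² × 30.63² / 22.55² = 28.93, so 29 per arm, as stated. For the loss allowance, 29 × 1.10 = 31.9 gives the stated 32; dividing by 0.90 gives 32.2, hence 33. That one-patient difference does not bear on this point. The calculation supplies the 32 and the 22.55 μm used below.

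**Inputs the documents do not give (assumptions).**
- k: number of experimental-arm patients who exit for severe adverse events. No event rate is stated.
- D: true mean CSFT change of those patients minus their imputed mean change. No value is stated.

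**Formula.** If only the experimental arm has such exits and all 32 are analysed with imputed values, the arm mean is wrong by (k/32) × D, and so is the difference between arms. A positive D means that the imputed values are too thin and atorvastatin looks better than it is.

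**Anchor for D.** Suppose a patient who stops loses the whole planned benefit while imputation still credits it. Then D = 22.55 μm:
- k = 1: (1/32) × 22.55 = 0.70 μm; 0.70 / 22.55 = 3%.
- k = 3: (3/32) × 22.55 = 2.11 μm; 2.11 / 22.55 = 9%.

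**Range.** Bias in μm, with percent of 22.55 μm in brackets:

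| k | D = 0 | D = 22.55 | D = 50 | D = 100 |
|---|---|---|---|---|
| 1 | 0 | 0.70 (3%) | 1.56 (7%) | 3.13 (14%) |
| 2 | 0 | 1.41 (6%) | 3.13 (14%) | 6.25 (28%) |
| 3 | 0 | 2.11 (9%) | 4.69 (21%) | 9.38 (42%) |

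The last two columns only show how the result scales; nothing in the documents supports those gaps.

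**Direction.** With exits in both arms, bias = (k_E/32) × D_E − (k_C/32) × D_C, where E is experimental and C is control. Equal counts and gaps cancel. More exits or a larger gap among controls reverses the sign.

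**Type I error.** The standard error of the difference is 30.63 × √(2/32) = 7.66 μm. A shift of 2.11 μm with no true effect raises the two-sided rate from 0.050 to 0.059. That needs a gap from some cause other than lost benefit, since an ineffective drug has no benefit to lose.

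**Precision.** Three exits are 3/32 = 9.4% of the arm and leave 29, which uses up that arm's allowance before any other loss. Even so, power with 29 against 32 observed is about 0.82. The issue is bias and lost safety information, not power.

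**The case against.** The strongest reply is that this is a condensed article. It says the full protocol is available on request, and follow-up after withdrawal and the imputation model are commonly left to that document or to an SAP. This stands for the imputation model: its absence is not a finding. It does not fully answer the point, because the article states a rule that groups severe adverse events with two ways of leaving the trial, and that wording should be put right where it stands.

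Other objections hold and limit the claim:

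- A reader might infer that every severe event leads to exit. The text refers to a decision, so withdrawal is discretionary.
- A reader might infer that the safety outcome loses the severe events themselves. The triggering event is recorded; only what follows it is lost.
- A reader might infer that the comparison is certainly biased in favour of atorvastatin. Injection-related exits can occur in either arm, and if atorvastatin reduces recurrence as hoped, controls would have more injections and possibly more such exits. Imputation also biases the result only if its assumption fails for these patients. With SD-OCT monthly, the model could use each patient's own earlier CSFT.
- A reader might infer a bias of 21% to 42% of the planned effect by assuming three exits and a gap of 50 to 100 μm. That gap is more than twice to over four times the whole planned benefit and has no source. The 100 μm in the Re-injection criteria is a trigger at a visit, not an expected mean gap at month 12. Lost benefit implies about 22.55 μm.
- Sensitivity analyses for missing data are already planned, although the article does not state what departure from the main assumption they cover.

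**Conclusion.** The concern holds in limited form. As written, item (3) does not separate stopping study treatment from stopping data collection. Followed literally, it gives up CSFT and safety observations that could have been made, in a way that may differ by arm because only one arm takes atorvastatin. The CSFT comparison may therefore be biased, with direction not certain, and safety follow-up after the triggering event is incomplete.

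The size cannot be derived from the documents. On the assumptions that exits occur only in the experimental arm, number one to three, and have a gap equal to the planned benefit, the bias is 0.7 to 2.1 μm, or 3% to 9% of 22.55 μm. It grows in proportion to either quantity and vanishes if the imputation is right on average for these patients. This is a modest effect on the primary result. The change is worth making because it replaces an untestable assumption with data at little cost.

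**What to change.** Reword item (3), rather than delete it, so that it refers to discontinuing study treatment because of a severe adverse event. Add that such patients continue the assessments already scheduled in Table 1 and the Follow-up plan (BCVA, SD-OCT, adverse events, injection count) to month 12 unless they withdraw consent. State that they are analysed as randomised with their observed data, and that imputation is used only for visits truly unobserved. Let the missing-data sensitivity analyses already planned include an arm-specific departure from missing at random, for example a shift applied to imputed CSFT in the experimental arm over a stated range.

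When and whether treatment is stopped is unchanged, and no view is taken on it here.

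The cost is an amendment to the protocol and, where needed, the consent wording, plus attendance by a few patients at visits already on the schedule. The estimated effect will be slightly diluted relative to an on-treatment effect, because patients who stopped are counted with their actual outcomes. The article reports 14 of 64 patients recruited at manuscript submission and describes an amendment route. The change helps only with exits that occur after it takes effect.

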### Methodology

A prospective, randomized controlled clinical trial will be conducted at Nanjing Lishui People’s Hospital. Patients diagnosed with branch or central RVO-ME and CP will be enrolled in this study. They will be randomly allocated in a 1:1 ratio to the control and experimental groups. The study design is illustrated in Fig. 1.

**Fig. 1 Fig1:**
[figure not shown]
Study design. PRN, pro re nata; RVO, retinal vein occlusion; ME, macular edema; CP, carotid plaque; BCVA, best corrected visual acuity; CSFT, central subfield thickness

### Randomization

Patients will be randomly divided into two groups in a 1:1 ratio using SPSS (Statistical Package for Social Sciences, version 26.0, IBM, Armonk, NY, USA). An independent investigator will generate a random sequence and allocate interventions.

### Masking

Patients and clinicians will be blinded after assignment. The implementation and maintenance of the randomization and masking methods will be completely validated. To avoid evaluation bias, the treatment groups will be hidden from the ophthalmologist who collects the clinical data during each follow-up period. Analysts dealing with the data will also be masked.

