### Follow-up plan

Monthly follow-ups and necessary re-examinations after surgery will be conducted. BCVA, slit lamp, intraocular pressure, indirect ophthalmoscopy, and SD-OCT will be performed at each visit. Blood biochemistry and carotid Doppler ultrasonography will be performed every 3 months. Routine blood tests, FFA, and electrocardiograms will be performed every 6 months. Infection measurements (HIV, hepatitis B and C, and syphilis) and chest CT will be performed during the last visit. The number of injections and the incidence of complications will be recorded and evaluated at each follow-up.

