### Re-injection criteria

If the BCVA drops by more than five Early Treatment Diabetic Retinopathy Study (ETDRS) letters (one line) or an increment in CSFT of 100 μm (or a 10% increment from the previous visit), intravitreal re-treatment will be performed.

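### Patients and clinicians are said to be blinded, but only one arm takes a daily oral drug and no placebo is described; as written, only assessor and analyst masking is supported

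*Protocol article*

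**What the plan says.** The Masking section makes three claims. The first is general: "Patients and clinicians will be blinded after assignment". The second concerns outcome assessment: "the treatment groups will be hidden from the ophthalmologist who collects the clinical data during each follow-up period". The third concerns analysis: "Analysts dealing with the data will also be masked". The section also promises that the randomization and masking methods will be fully validated, but it names no method for masking patients.

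The arms are defined in the Abstract and again under Trial design. For control: "The control group will be treated with intravitreal conbercept monthly for 3 months", then monthly evaluation with injection as needed. For the other arm: "the experimental group will be treated with oral atorvastatin 20 mg daily combined with the control group treatment". Trial design gives manufacturer and approval details for conbercept and atorvastatin and lists no third product.

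The primary outcome is change in CSFT from baseline to 12 months. Secondary outcomes are BCVA, number of injections and adverse events. Under Re-injection criteria, re-treatment follows a BCVA loss of more than five letters, or a CSFT rise of 100 μm or of 10% since the previous visit.

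**The concern.** The arms differ only in a daily oral drug that one arm takes and the other does not. Without a matching placebo, a patient cannot be unaware of this, and neither can the person who prescribes it. The first masking claim therefore conflicts with the arm definitions.

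Three things are at stake:

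- **BCVA.** Letter scores depend on effort, and a patient who knows the arm may try harder or less hard. BCVA counts twice, as a secondary outcome and as a trigger for re-injection.
- **Injections and CSFT.** A changed BCVA reading can change a re-injection decision. That alters the injection count directly and can alter month-12 CSFT indirectly.
- **Adverse events.** The safety section lists gastrointestinal discomfort among drug-related events and has possible causes recorded. Reporting by patients who know what they take is open to expectation, and discussing causes can disclose the arm.

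A trial reported as blinded to patients and clinicians would also lead readers to judge its risk of bias too favourably.

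**Working it through.** The masking claim contains no figure, so the main check is to compare each claim with what the article describes.

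| Who | Masking claimed? | Means described? | Supported as written? |
|---|---|---|---|
| Patients | Yes | None; only one arm takes a daily oral drug | No |
| Prescriber of atorvastatin | Yes, as a clinician | None | No |
| Ophthalmologist collecting data | Yes | Group hidden at follow-up | Yes, unless patients disclose |
| Person deciding on re-injection | Only as a clinician | Not identified | Cannot be told |
| Analysts | Yes | Stated | Yes |

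**Route from unmasking to outcomes.** Patient knowledge → BCVA effort → BCVA limb of the re-injection rule → number of injections → CSFT. The first two links need only an unmasked patient. The CSFT limb of the rule rests on SD-OCT and is much less exposed.

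**The plan's own figure.** Sample size per group = 2 × (1.96 + 0.84)² × 30.63² / 22.55² = 28.93, rounded up to 29 as stated. It does not depend on masking, and correcting the masking text leaves it unchanged.

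**Scale, as illustration only.** The article gives no estimate of how far unmasking would shift any outcome. For the injection count, take the SDs that the Introduction cites for conbercept over 9 months (1.39 in central RVO, 1.90 in branch RVO) and 29 patients per arm. Assume no true effect and a shift *b* in mean injections caused purely by unmasking. Then SE = SD × √(2/29), which is 0.365 or 0.499. The chance of a two-sided 5% rejection is Φ(b/SE − 1.96) + Φ(−b/SE − 1.96).

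| Assumed shift *b* | SD 1.90 | SD 1.39 |
|---|---|---|
| 0 | 5% | 5% |
| 0.25 | 8% | 11% |
| 0.5 | 17% | 28% |
| 1.0 | 52% | 78% |

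The shifts are assumptions, and the SDs come from a 9-month study rather than this 12-month trial. The table shows only that a shift of half an injection would not be negligible. It does not show that such a shift will occur.

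**The case against.** The strongest reply is that this is a condensed article. The full protocol is available on request, and a placebo might be described there. That stands as far as it goes: the article supports saying that no placebo is described, not that none exists. It does not remove the contradiction. The control regimen is set out in full, and a dummy tablet would be part of it.

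Second, the clinician claim may be partly recoverable. An independent investigator allocates interventions and might also supply the drug, leaving the retinal team masked. The data-collecting ophthalmologist is already said to be masked, BCVA and SD-OCT are collected at the same visits, and the re-injection rule is numeric. A reader might infer that an unmasked clinician will inject at discretion. The article does not say so: re-treatment follows stated criteria. What stands is that the decision-maker is not identified.

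Third, the schedule states "Blood biochemistry and carotid Doppler ultrasonography will be performed every 3 months", and a reader might infer that lipid results will reveal the arm. Lipids are never named, and nothing says the masked ophthalmologist sees laboratory results. This route is conjecture and forms no part of the point.

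Fourth, the primary outcome is an instrument measurement, so its exposure is indirect. Direction matters too. Fewer injections in one arm would favour it on injection count but would tend to count against it on CSFT. Differential re-injection therefore need not favour the same arm on both. Both arguments limit the consequence for CSFT, but they do not protect BCVA or patient-reported adverse events.

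**Conclusion.** The point holds. The statement that patients and clinicians are blinded is contradicted by the article's own arm definitions, for patients and for whoever prescribes atorvastatin. Masking of the data-collecting ophthalmologist and of the analysts is supported.

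As described, the contradiction covers all 64 planned patients. The conclusion is conditional on the full protocol containing no matching placebo. BCVA and patient-reported adverse events are exposed directly. The injection count is exposed through the BCVA trigger, and CSFT only indirectly.

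The size of any bias cannot be derived from the document. A reader might set the hypothesised CSFT difference of 22.55 μm against the effect of a few altered injections and conclude that a given share of it could be artefact. The article gives neither the share of decisions that would change nor their effect on CSFT, so no such fraction is supported. It is likewise unsupported to say that masking of any kind is impossible.

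**What to change.** First establish whether the full protocol has a matching placebo. If it does, describe it in the Masking and Trial design sections. If it does not:

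1. Replace the first sentence of Masking with: open-label to patients and prescribers; masked BCVA examiner, OCT measurement and analyst.
2. State that the already-masked ophthalmologist applies the existing re-injection criteria to that visit's BCVA and OCT, and records the result before any unmasked contact.
3. Ask patients not to mention tablets at assessments.
4. Report the trial as assessor-masked.

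The re-injection criteria, treatments and sample size stay unchanged, and safety review of laboratory results stays as planned. The cost is an amendment by the article's own route (notification of sponsor and funder, and a registry update) plus a visit-flow instruction. Fourteen patients had been recruited at submission, so the report should say under which arrangement their early visits took place. The downside is a weaker masking claim, but a true one. Patients remain unmasked, so residual bias in BCVA effort and in adverse-event reporting should be acknowledged.
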